### Anxiety and Depression

Symptoms of anxiety and depression are measured using the Hospital Anxiety and Depression Scale (HADS) questionnaire [34]. HADS is a 14-item self-reported questionnaire consisting of two 7-item subscales measuring anxiety and depressive symptoms (ie, it does not assess somatic symptoms). Each item is scored on a four-point Likert Scale from 0 to 3. Scores are tabulated for each subscale, resulting in a score of 0-21, with higher scores indicating higher levels of anxiety or depressive symptoms. The measures from HADS are compared between groups at baseline, 6 months, and 12 months.

### Health and eHealth Literacy

Patients’ health and electronic health (eHealth) literacy skills are measured using a Danish validated version of the eHealth literacy assessment toolkit (eHLA) [35] and the eHealth Literacy Questionnaire (eHLQ) [36]. The eHLA is a toolkit used to assess health literacy and digital literacy. The toolkits consist of seven tools, four health related and three digitally related, that are either self-reported, such as questionnaires, or a performance test of relevant skills [35]. The eHLQ is a 35-item 7-scale questionnaire used to evaluate and understand how patients interact with digital health services [36]. The measurement of health and eHealth literacy skills is compared between groups at baseline, 6 months, and 12 months.

**Table 1 table1:** Primary and secondary outcomes.

Outcome and measurement		Time of measurement					Group	
		Baseline	6 months	12 months	End of study	Continuous	Intervention	Control
**Primary**								
	Quality of life	✓	✓	✓			✓	✓
**Secondary**								
	Development of clinical data in intervention group			✓		✓	✓	
	Illness perception	✓	✓				✓	✓
	Type of motivation	✓	✓	✓			✓	✓
	Anxiety and depression	✓	✓	✓			✓	✓
	Health and eHealth^a^ literacy	✓	✓	✓			✓	✓
	Patients’ experiences		✓	✓			✓	
	Economic evaluation				✓		✓	✓

^a^eHealth: electronic health.

### Use of and Experiences Using the HeartPortal

Qualitative exploration of patients’, their relatives’, and health care professionals’ experiences using the HeartPortal will be conducted. Semistructured interviews inspired by Brinkman and Kvale [37] will be conducted after 6 months and 12 months. To analyze which parts of the HeartPortal are being used and for how long, time log files for login/logout of patients and relatives will be analyzed. The patients and relatives will be asked for their consent to extract their log files from the database for analysis.

### Economic Evaluations

A cost-effectiveness analysis will be based on the guidelines for economic evaluation by Drummond et al [38]. Estimates of the mean costs per patient will be made with a broad societal perspective, including use of resources for patients, hospital, and municipality. Estimation of costs will be based on data at the patient level for all patients, both at the intervention and control groups.

### Data Analysis

All demographic data are being stored in the Future Patient database (FPD). Data from questionnaires are stored in Research Electronic Data Capture software [computer software] (Nashville, TN: Vanderbilt University) and used for quantitative analysis.

### Adverse Events and Dropout

All adverse events, including deaths, dropouts, or withdrawals from the study will be recorded and documented. If the patients no longer want to participate in the study, they can withdraw their consent at any time, and the reason for withdrawal will be documented. In this case, the project team will collect the equipment upon request. Patients who do not participate actively in the intervention will still be included in the study and analyzed according to the intention-to-treat approach. These patients will be allowed to retain use of the project equipment for as long as they want. Technical problems with the equipment will be recorded and documented.

### Statistical Analysis

At baseline, descriptive statistics [39] will be reported as median with 25th-75th percentiles in the case of skewed distribution or mean (SD) for normally distributed continuous variables. The nonparametric Kolmogorov-Smirnov test will be used to investigate normality of the distribution. An intention-to-treat analysis on all the randomized subjects will be conducted to provide unbiased comparisons between the intervention and control groups in order to avoid the effects of dropout.

The analysis of change in QoL, anxiety and depression, self-determination, illness perception, type of motivation, and health and eHealth literacy tests will be performed using data acquired through questionnaires. Comparison of incidence rates will be used to investigate the differences between the intervention and control groups. Two-sided tests and a significance level of 0.05 will be used.

All events from the day after randomization to patient exit will be included, while any other evident outcomes will be measured as changes from baseline to all assessment time points. Changes in the other evident outcomes will be tested using linear mixed models. Linear mixed models allow repeated measures to be collected in a longitudinal design and are superior when dealing with dropouts compared to other methods used for repeated measures. Hence, it will not be necessary to use imputation techniques on missing data. Statistical analyses will be performed using SPSS [computer software] (version 25.0. Armonk, NJ: IBM Corp), and values of *P*<.05 will be considered significant for all tests.

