### Eligibility Criteria

The target group in this study consists of patients diagnosed with heart failure according to the New York Heart Association (NYHA) class I-IV [27]. Patients with heart failure are recruited from the Cardiology Wards at hospitals in Skive, Viborg, Silkeborg, and Randers, all situated in the central region of Jutland, Denmark. The inclusion criteria are that the patient must have had a heart failure–related hospitalization within the past 2 weeks; have a stable internet connection at home; and have the ability to sign an informed consent form. Patients may have a pacemaker, and a maximum of 20% of the target group may belong to NYHA class I. Exclusion criteria are a revascularization or open-heart surgery within 3 months prior to inclusion; presence of previous neurologic, musculoskeletal, or cognitive disability or active psychiatric history (as noted in the medical record) other than depression or anxiety related to cardiac or other chronic illness; and absence of basic Danish language skills. All data from the recruitment process and patient withdrawal or dropout will be documented in a consort diagram.

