### Illness Perception

Changes in illness perceptions are being evaluated for both groups using the Brief Illness Perception Questionnaire (Brief IPQ) [32]. The Brief IPQ is a nine-item scale questionnaire designed to rapidly assess the cognitive and emotional representations of illness. Five of the items assess cognitive illness representation, two items assess emotional representation, and one item assesses illness comprehension. The last item is a causal question that asks the patient to list the three most causal factors in their illness. All items except one, the causal question, are scored on a scale from 0 to 10. The measure of the Brief IPQ is compared between groups at baseline, 6 months, and 12 months.

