### Type of Motivation

Changes in the type of motivation are measured using the Health Climate Change Questionnaire (HCCQ) [33]. The HCCQ is a 15-item questionnaire that assesses patients’ perceptions of the degree to which their health care providers are supportive of their autonomy. Respondents rate each statement on a seven-point Likert scale (from “Not at all true” to “Very true”). The total score is calculated by averaging the values of each item. The HCCQ can be used in its full version (15-items) or short version (6-items). In this study, the full version is used. The scores from HCCQ are compared between groups at baseline, 6 months, and 12 months.

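### The mixed models test change from baseline with no stated adjustment for the baseline score; adding it would gain precision at no cost

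*Protocol article*

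**What the plan says.** The Statistical Analysis section of the protocol article introduces "The analysis of change in QoL, anxiety and depression, self-determination, illness perception, type of motivation, and health and eHealth literacy tests" as resting on questionnaire data. It then separates events from everything else: apart from events, "any other evident outcomes will be measured as changes from baseline to all assessment time points". The method follows directly: "Changes in the other evident outcomes will be tested using linear mixed models". Quality of life, the primary outcome, is in the list of outcomes analysed as change.

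No model terms are named: no arm, visit, interaction or covariate. The baseline score is neither put in nor ruled out.

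The Quality of Life section and Table 1 show that the KCCQ is collected at baseline in both arms. The secondary questionnaires also have a baseline measurement in both arms.

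Four secondary sections go further and list baseline among the times at which the arms are contrasted:
- Illness Perception: "The measure of the Brief IPQ is compared between groups at baseline, 6 months, and 12 months"
- Type of Motivation: "The scores from HCCQ are compared between groups at baseline, 6 months, and 12 months"
- Anxiety and Depression: "The measures from HADS are compared between groups at baseline, 6 months, and 12 months"
- Health and eHealth Literacy: "The measurement of health and eHealth literacy skills is compared between groups at baseline, 6 months, and 12 months"

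The Quality of Life section says nothing of this kind about the KCCQ. The Statistical Analysis section presents baseline statistics as descriptive.

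**The concern.** A change score subtracts the whole baseline value, as if follow-up tracked baseline one for one. When the correlation is below 1, that over-corrects and adds noise. Regressing on baseline uses the coefficient that the data support, and with equal SDs at the two times it is more precise at every correlation below 1.

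The loss is largest when baseline predicts follow-up poorly, and there is reason to think that could happen here. Eligibility requires that "the patient must have had a heart failure–related hospitalization within the past 2 weeks", a medication titration phase of up to 3 months comes next, and the follow-up scores are taken at 6 and 12 months. A score taken soon after an admission may be only a moderate guide to one taken half a year or a year later.

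What is at stake is the width of the confidence interval for the primary outcome and each questionnaire outcome, in a trial planned on 63 evaluable patients per arm. A smaller matter is that contrasting randomised arms at baseline can reveal only chance differences if randomisation was sound.

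**Working it through.** **Inputs from the Power Calculation and Statistical Analysis sections.** Difference 10 KCCQ points; power 80%; 63 per group; 10% dropout; 140 in total; two-sided 0.05; equal allocation.

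**Inputs not given, so assumed.** The SD, and the correlation rho between baseline and follow-up (shown at 0.3, 0.5 and 0.7). SDs are taken as equal at both times and in both arms.

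**Step 1: the plan's own figure.** n per group = 2 × SD² × (1.96 + 0.842)² / 10². With SD 20 this is 2 × 400 × 7.85 / 100 = 62.8, so 63. Any SD from about 19.88 to 20.03 gives 63. Dropout: 63 / 0.9 = 70 per group, 140 in total. The stated numbers therefore fit an SD of 20, but that value is inferred. The article does not say whether it would be the SD of a score at one time or the SD of a change.

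**Step 2: relative precision.** With σ the SD at one time point:
- variance of change = 2σ²(1 − rho)
- variance after baseline adjustment = σ²(1 − rho²)
- ratio adjusted/change = (1 − rho²) / [2(1 − rho)] = (1 + rho)/2

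The ratio is 0.65 at rho 0.3, 0.75 at 0.5, 0.85 at 0.7 and 0.90 at 0.8. The same ratio applies to the sample size needed.

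**Step 3: power at 63 per group for 10 points.** Power = Φ(10 / [SD × √(2/63)] − 1.96), with √(2/63) = 0.178.

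Case A, SD 20 at a single time point. SD of change = 20√[2(1 − rho)]; adjusted SD = 20√(1 − rho²).

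| rho | Power, change | Power, adjusted | n per group, change | n per group, adjusted |
|---|---|---|---|---|
| 0.3 | 66.0% | 83.7% | 88 | 58 |
| 0.5 | 80.1% | 90.0% | 63 | 48 |
| 0.7 | 95.2% | 97.6% | 38 | 33 |

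Case B, SD 20 is the SD of change. Adjusted SD = 20√[(1 + rho)/2].

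| rho | Power, change | Power, adjusted | n per group, change | n per group, adjusted |
|---|---|---|---|---|
| 0.3 | 80.1% | 93.6% | 63 | 41 |
| 0.5 | 80.1% | 90.0% | 63 | 48 |
| 0.7 | 80.1% | 86.1% | 63 | 54 |

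Over rho 0.3 to 0.7 the power forgone is about 2 to 18 percentage points in case A and 6 to 14 in case B. The change score falls below the planned 80% only in case A with rho under 0.5.

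**Step 4: chance imbalance.** Given an observed baseline difference d between arms, the change-score estimate is expected to shift by −(1 − rho)d. With a single-time SD of 20, one standard error of d is 20 × 0.178 = 3.6 points, so the shift is 0.7 × 3.6 = 2.5 points at rho 0.3 and 0.5 × 3.6 = 1.8 at rho 0.5. It averages to zero over randomisations. Baseline adjustment removes it from the one trial that is run.

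**Step 5: does another natural reading avoid the loss?** Suppose baseline enters the mixed model as one more response visit with free arm means. With complete data, the arm-by-visit contrast is then the unadjusted difference in change, and precision is the same as for the change score. The loss is avoided only by a baseline covariate or a common baseline mean, and neither is stated.

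**The case against.** The strongest reply is that silence is not exclusion. The section names no model terms at all, so nobody can conclude that baseline has been left out. A mixed model of change with the baseline score, by visit, as a covariate fits the wording and gives the same arm effect as modelling the follow-up score. A covariate list is commonly left to the analysis plan, which is not shown. This stands: a reader might infer that baseline adjustment was rejected, and the text does not support that. What remains is that the article does fix the quantity to be tested, and that quantity is efficient only with a term it does not mention.

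A reader might also infer that the trial is underpowered. The documents do not support that either. The SD of 20 is back-calculated, and the Power Calculation section speaks of an increase or improvement, so an SD of change is at least as natural a reading. On that reading the change score delivers the planned 80% at any correlation. Even on the other reading there is a shortfall only if rho is below 0.5, and the gap is small at 0.7.

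Nor is the comparison biased. Under randomisation an unadjusted change score is a valid comparison with the right type I error.

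Finally, a reader might take the plan to test the arms at baseline on every questionnaire. The text says only that they are compared, for four secondary sets and not the KCCQ. The 0.05 threshold governs tests that are done and does not commit anyone to baseline tests. Such comparisons would not cost power in any case.

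**Conclusion.** The point holds as lost efficiency. The article fixes change from baseline as the tested quantity for the questionnaire outcomes, including the primary, and states no adjustment for a score that it already collects. If the change score is left unadjusted, its variance exceeds that of the adjusted estimate by a factor of 2/(1 + rho), which is 1.54 at rho 0.3, 1.33 at 0.5 and 1.18 at 0.7. The direction needs only equal SDs at the two times and rho below 1. The power figures rest further on the inferred SD of 20, on which SD that is, and on the assumed range of rho. They show what adjustment could add; they do not show that the planned power is missed.

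The baseline comparisons of the four secondary sets are a separate, minor matter of wording. This is a free improvement, not an error in the plan.

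**What to change.** In the Statistical Analysis section, and in the analysis plan, state that the linear mixed model for each questionnaire outcome includes the baseline score and its interaction with visit as covariates, alongside arm, visit and arm-by-visit. A constrained longitudinal model, with baseline among the responses and a common baseline mean for both arms, would serve equally well. If the analysis plan already says this, the article needs only to say so.

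In the sections on illness perception, motivation, anxiety and depression, and health and eHealth literacy, remove baseline from the times at which groups are compared. Describe baseline scores by arm without testing, in line with the descriptive treatment in the Statistical Analysis section.

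The cost is one sentence on the model and four small wording edits. No new data, visits or patients are needed. The change should be fixed before outcome data are examined by arm.

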### Conclusions

The expected outcomes are increased quality of life, increased motivation and illness perception, reduced anxiety and depressions, improved eHealth literacy, and health economics benefits. We expect the study to have a clinical impact for future telerehabilitation of patients with heart failure.

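### Every secondary questionnaire result with P<.05 counts as significant, with no order, gate or exploratory label, so the chance of a false-positive secondary finding is well above 5%

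*Protocol article*

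**What the plan says.** The Statistical Analysis section sets the threshold twice. It first states "Two-sided tests and a significance level of 0.05 will be used", and it ends by saying that P values below .05 "will be considered significant for all tests". The constructs covered are listed as "The analysis of change in QoL, anxiety and depression, self-determination, illness perception, type of motivation, and health and eHealth literacy tests". Outcomes other than events are to be "measured as changes from baseline to all assessment time points" and tested with linear mixed models.

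The outcome sections describe the secondary instruments:

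- Brief IPQ: nine items, of which "All items except one, the causal question, are scored on a scale from 0 to 10".
- HCCQ: one averaged total.
- HADS: two subscales.
- eHLA: "The toolkits consist of seven tools, four health related and three digitally related".
- eHLQ: "The eHLQ is a 35-item 7-scale questionnaire".

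Each of these sections plans group comparisons at baseline, 6 months and 12 months. Table 1, however, ticks illness perception only at baseline and 6 months.

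KCCQ quality of life is the single named primary outcome, and the sample size rests on it. The Conclusions section then says: "The expected outcomes are increased quality of life, increased motivation and illness perception, reduced anxiety and depressions, improved eHealth literacy, and health economics benefits".

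**The concern.** The plan fixes one reading for every secondary P value: below .05 is significant. It names no key score or time point for any instrument, sets no order among the secondaries, does not make them depend on the primary result, and calls none of them exploratory. Most of the secondary constructs also appear beside the primary in the list of expected benefits.

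Followed as written, a trial with a null KCCQ comparison could still report one literacy scale or one HADS subscale at one visit as a significant effect of the program. A reader would have no stated basis for discounting it as one result among many. What is at stake is how far secondary findings can be trusted, not the validity of the primary test.

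**Working it through.** **Reference figure.** The article states no family-wise error rate, so there is none to reproduce. The benchmark is the stated per-test level: 0.05 two-sided, which is 0.025 in the benefit direction.

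**Counting the scores** (Illness Perception, Type of Motivation, Anxiety and Depression, and Health and eHealth Literacy sections).

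- Fullest reading: Brief IPQ 8 + HCCQ 1 + HADS 2 + eHLA 7 + eHLQ 7 = 25 scores. At two post-baseline times, 25 × 2 = 50 tests.
- With the Brief IPQ at 6 months only, as in Table 1: 50 − 8 = 42 tests.
- One score per instrument, but both HADS subscales: 6 scores × 2 times = 12 tests.
- Smallest reading, one test per instrument: 5 tests.

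Incidence-rate comparisons and the clinical data collected in the intervention group are left out of all counts.

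**Formulas**, with no true secondary effect and m tests.

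- Independent tests: 1 − 0.95^m for any false positive, and 1 − 0.975^m for a false benefit. For m = 50: 1 − 0.95^50 = 0.923 and 1 − 0.975^50 = 0.718. For m = 5: 1 − 0.95^5 = 0.226 and 1 − 0.975^5 = 0.119.
- Equally correlated normal test statistics with correlation ρ and c = 1.96: 1 − ∫ [Φ((c − √ρ·u)/√(1−ρ)) − Φ((−c − √ρ·u)/√(1−ρ))]^m φ(u) du. For benefit only, drop the second Φ term.

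The article gives no correlations, so ρ is an assumption shown over a range.

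| Tests | Any direction: ρ = 0 | ρ = 0.5 | ρ = 0.8 | Benefit only: ρ = 0 | ρ = 0.5 | ρ = 0.8 |
|---|---|---|---|---|---|---|
| 50 | 92% | 62% | 30% | 72% | 32% | 15% |
| 42 | 88% | 58% | 28% | 65% | 29% | 14% |
| 12 | 46% | 32% | 19% | 26% | 16% | 9% |
| 5 | 23% | 18% | 13% | 12% | 9% | 6% |

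**A more structured correlation.** For 25 scores at two times, simulation (100,000 runs) with assumed correlations of 0.3 within instruments, 0.1 between instruments and 0.6 across time gives 87% in any direction and 56% for benefit. With 0.6, 0.4 and 0.7 it gives 68% and 36%.

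Every any-direction figure is above 5%, and every benefit-only figure is above 2.5%. The benefit-only figures fall on both sides of 50%, depending on the count and the correlation.

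**The case against.** The strongest reply is that handling of secondary multiplicity is usually left to the statistical analysis plan, which is not shown, and that a journal article need not spell it out. That would answer a complaint about silence. Here the article states a rule for all tests, and a later plan that ordered the secondaries or called them exploratory would have to depart from it.

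Other objections stand and limit the point:

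- The count of 25 scores at two times is an upper reading. The article describes the instruments but never says that each Brief IPQ item or each eHLA tool is tested, and a linear mixed model could give one overall test per score. This changes the size but does not bring the error rate down to 5%, as the five-test row shows.
- The outcomes are not without any hierarchy. One primary is separated from labelled secondaries, and testing the secondaries does not inflate the primary error rate. The 0.05 is a per-test level, and the article promises no family-wise control.
- The benefits in the Conclusions are expectations, not criteria for declaring success, and that list names eHealth literacy but not health literacy.

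A reader might infer that a false secondary benefit is more likely than not. The documents do not support this. Half of two-sided false positives point against the intervention. The benefit-only chance passes 50% only with many tests and little or no correlation (28 or more if independent), and the article fixes neither.

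**Conclusion.** The point holds as one about how secondary results may be interpreted. The stated rule lets any chance-positive secondary score be reported as significant, whatever the KCCQ result. In either direction, the chance of at least one such result is 62% to 92% for 50 tests (ρ from 0.5 to 0; 30% at ρ = 0.8), 19% to 46% for 12 tests and 13% to 23% for 5 tests (both for ρ from 0.8 to 0). For a false benefit alone it is 32% to 72% for 50 tests (ρ from 0.5 to 0; 15% at ρ = 0.8) and 6% to 12% for 5 tests.

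These figures assume no true secondary effect, the test counts above and equally correlated test statistics. The number of tests and the correlation are not in the article. The primary analysis is sound in this respect. The matter should be corrected, but it does not threaten the trial's main conclusion.

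**What to change.** In the Statistical Analysis section, replace the closing rule on P values with wording such as:

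> *The two-sided 0.05 level applies to the primary KCCQ comparison; secondary questionnaire outcomes are exploratory and reported as between-group differences with 95% confidence intervals, without claims of statistical significance.*

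Bring the earlier statement of the 0.05 level in the same section into line with this.

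If confirmatory secondaries are wanted, name one score and one time point per construct. Test them in a fixed order or with Holm's procedure, only if the primary is significant, and label the rest exploratory. The paragraph on expected outcomes can stay as it is.

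The change needs no extra patients or data and takes no power from the primary comparison. Its cost is that an isolated secondary P<.05 can no longer be presented as a demonstrated benefit.
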